### Inclusion, exclusion, and termination criteria

2.3

Inclusion criteria: Community population aged 18 years or older with informed consent. The threshold of 18 years is selected to encompass a broader spectrum of glaucoma types beyond typical age-related cases, such as juvenile and secondary glaucoma.

Exclusion criteria: (1) Inability to complete the questionnaire or comply with long-term follow-up; (2) Inability to undergo IOP measurement or fundus photography due to poor cooperation, low compliance, or coexisting ocular pathologies (such as corneal opacities, advanced cataracts, or vitreous opacities); (3) Presence of other ocular conditions that could confound the definitive diagnosis of glaucoma, such as retinitis pigmentosa or status post panretinal photocoagulation (PRP).

Termination criteria: When study participants in any group are diagnosed with glaucoma through screening or self-visit, they will be recorded and removed from the screening program. These patients will be enrolled in a chronic disease follow-up management to monitor disease progression and assess its impact on quality of life.

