This screening tool will underpin a proposed three-tiered strategy for glaucoma screening. Tier 1 Screening (Primary Screening): The pre-designed risk assessment questionnaire is administered within the community to identify high-risk individuals. Tier 2 Screening (Secondary Screening): These high-risk individuals undergo a combination of screening tests, including visual acuity, IOP measurement, fundus photography, and ocular optical biometry, which will be conducted at community healthcare or primary care centers. This stage is augmented by AI-assisted image interpretation to identify subjects suspected of having glaucoma. Tier 3 Screening (Tertiary Screening): A definitive diagnosis of glaucoma is established within the ophthalmology department of a tertiary hospital.

In the Tier 2 screening stage, fundus photographs will be interpreted using the Airdoc glaucoma-specific AI automatic screening system, which is built on a deep convolutional neural network algorithm employing an integrated multi-task learning architecture for simultaneous segmentation and classification. Standardized and traceable glaucoma grading decision rules have been established and fully integrated into the screening workflow. The system automatically performs image preprocessing, precise optic disc detection, quantitative analysis of optic disc morphology, segmentation of the optic cup and retinal nerve fiber layer defect (RNFLD) regions, and identification of glaucomatous lesions including localized RNFLD, diffuse RNFLD, optic disc hemorrhage, and optic cup notching. Moreover, it also calculates horizontal and vertical cup-to-disc ratios, ultimately generating a quantitative glaucoma risk score and a graded recommendation.

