### Grouping schemes

2.4

According to the cluster randomized study design, each community serves as a cluster. The statistician uses a computer-generated random sequence to independently and with equal probability assign each cluster to one of the three groups (simple cluster randomization): (1) blank control group (no screening group), (2) routine screening group, and (3) tiered screening group. To set up blank controls can analyze the clinical significance and health economic value of routine screening mode for the early diagnosis and treatment of glaucoma. On this basis, it is sufficient to compare the difference in efficiency and cost-effectiveness between the routine screening mode and the tiered screening mode. Baseline data and follow-up outcomes are collected uniformly for all participants.

The control group (no screening group) does not undergo any glaucoma screening, and the study subjects can detect and confirm glaucoma through active medical visit or opportunistic screening. The routine screening group is screened with IOP measurement combined with fundus photography to detect glaucoma. The three-tiered screening model designed in this study is adopted in the tiered screening group. It is expected that high-risk populations of glaucoma are identified in the tier 1 screening, who will enter the tier 2 and/or 3 screenings to diagnose or exclude glaucoma (Figure 1).

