**Figure 1 fig1:**
[figure not shown]
Methodology flowchart of the study. AI, artificial intelligence.

The screened high-risk populations, suspected patients, and diagnosed glaucoma patients from all the three groups will receive standard glaucoma treatment and AI-assisted intelligent follow-up of chronic disease management, including health education, subsequent visit reminders and medication guidance, so as to expand the coverage and reduce the labor cost of follow-up.

A no-screening control arm is included in this study, in which participants will not receive any ophthalmic examinations actively provided by the study protocol. As the study population consists of community-dwelling individuals rather than confirmed patients, the absence of active screening does not pose additional disease-related risks to the participants. Subjects in the control arm remain free to seek medical attention if symptoms arise or to undergo opportunistic screening through routine healthcare encounters. Therefore, enrollment does not restrict their access to external medical services or affect their standard of care.

To strengthen the ethical justification for the no-screening control group, the following safeguards will be implemented: (1) Regular glaucoma-related health education and disease awareness sessions will be provided to the control group throughout the study period to help participants recognize early symptoms and understand the potential harms of glaucoma, thereby enhancing their capacity for self-monitoring and healthcare-seeking behavior. (2) A structured annual follow-up protocol will be established to collect health status data from the control arm via standardized questionnaires or digital platforms, with particular attention to monitoring symptoms such as visual acuity changes or ocular discomfort, and systematically recording any ophthalmology visits initiated by participants, including the reasons for consultation, examinations performed, and resulting diagnoses. (3) At the end of the study period, a comprehensive ophthalmic screening will be uniformly offered to all participants in the control arm to compensate for the opportunity loss resulting from the absence of regular screening during the study. (4) Periodic reports on study progress and participant health status will be submitted to the Ethics Committee to ensure ongoing adherence to ethical standards, with measures adjusted as necessary based on emerging circumstances.

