### Follow-ups and outcome variables

2.6

Commencing at study initiation, participants will be prospectively followed up annually for a minimum of 6 years. Data will be collected yearly through IOP measurements, fundus photography, and follow-up questionnaires (Table 1). For patients with suspected or confirmed glaucoma, additional data will be collected including ocular optical biometry, RNFL thickness, and automated perimetry. Long-term follow-ups will track annual incidence and blindness rates of glaucoma, and quality of life among glaucoma patients.

**Table 1 tab1:** Follow-up schedule.

Groups		Visit number	0	1	2	3	4	5	6
		Visit time (year)	Baseline	1	2	3	4	5	6
No screening group		Questionnaire	×	×	×	×	×	×	×
Routine screening group		Questionnaire	×	×	×	×	×	×	×
		Intraocular pressure	×			×			×
		Fundus photography	×			×			×
Tiered screening group	High-risk population	Questionnaire	×	×	×	×	×	×	×
		Intraocular pressure	×	×	×	×	×	×	×
		Fundus photography	×	×	×	×	×	×	×
		Glaucoma specialist examination	Performed according to the screening results						
	Non-high-risk population	Questionnaire	×	×	×	×	×	×	×
		Intraocular pressure							
		Fundus photography							

All primary outcome measures will be analyzed on a per-participant (per-person) basis. The main endpoint of this study is glaucoma detection rate of the screening protocol, with sensitivity and specificity of the screening included as additional primary outcome measures. Glaucoma detection rate is defined as the proportion of participants in each arm with a final confirmed diagnosis of glaucoma in at least one eye, as determined by the reference standard examination in the screening arms or by passive case-finding through medical records in the control arm. Sensitivity is defined as the proportion of participants with confirmed glaucoma in at least one eye (as determined by the reference standard comprehensive ophthalmic examination) who are correctly identified by the screening protocol. Specificity is defined as the proportion of participants with no glaucoma in either eye who are correctly classified as negative by the screening protocol.

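### Exclusion criterion 2 depends largely on eye tests that the three arms receive to different extents, so it can remove people at different rates by arm and inflates sensitivity.

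*Protocol article*

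**What the plan says.** Three parts of the protocol article bear on this.

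- **Eligibility (section 2.3).** Criterion 2 excludes for "Inability to undergo IOP measurement or fundus photography due to poor cooperation, low compliance, or coexisting ocular pathologies", with corneal, lens and vitreous opacities as examples. Criterion 3 excludes for "Presence of other ocular conditions that could confound the definitive diagnosis of glaucoma".
- **Who is examined (sections 2.2 and 2.4, Table 1 in 2.6).** For the routine arm: "The routine screening group is screened with IOP measurement combined with fundus photography to detect glaucoma". In the tiered arm only questionnaire-positive people reach the tests: "These high-risk individuals undergo a combination of screening tests, including visual acuity, IOP measurement, fundus photography, and ocular optical biometry". In Table 1 the rows for pressure and photography under "Non-high-risk population" are empty. In the control arm "participants will not receive any ophthalmic examinations actively provided by the study protocol", and Table 1 lists only the questionnaire there.
- **Denominator (section 2.6).** The main endpoint is the share of each arm's participants with confirmed glaucoma. Sensitivity and specificity are additional primary outcomes.

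Two general sentences point the other way. Section 2.4 states: "Baseline data and follow-up outcomes are collected uniformly for all participants". Section 2.6 opens by describing annual pressure measurement and photography without distinguishing arms. Neither agrees with Table 1 or with the description of the control arm.

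**The concern.** Whether a person can complete tonometry or give a usable photograph is mostly learned by trying. Tests scheduled by arm can be tried only once the arm is known, and only in the people to whom that arm gives them. The article describes no eligibility examination common to all arms, and no rule for judging criterion 2 from history or records alone. Followed as written, the criterion acts on everyone in one arm, on part of the second, and in the third only through what is already known.

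Two things are at stake. First, the randomised comparison of detection rates would rest on populations selected to different degrees. Second, failed tests are a real limitation of community screening. If the people concerned are removed as ineligible, their undetected glaucoma leaves the sensitivity denominator, and a primary outcome looks better than the programme would perform in use.

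**Working it through.** **The plan's own figures.** Section 2.5 assumes 3.54% detected under routine and 4.54% under tiered screening. The continuity-corrected two-proportion formula gives 6,283 per arm, as stated. The design effect is 1 + 39 × 0.005 = 1.195, rounded to 1.20. Then 6,283 × 1.20 = 7,540; 7,540 / 0.80 = 9,425; and × 3 = 28,275. The sample size reproduces and is not at issue. It supplies the 3.54% and the 1.0-point difference used below.

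**Inputs the documents do not give (assumptions).** Share unexaminable, u: 5% or 10%. Their glaucoma prevalence relative to the average, k: 2 or 3. Share of them classed high-risk: one half. Every examinable case is detected in both screening arms, so the strategies do not truly differ and any gap is an artefact of the exclusion.

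**Formulas**, per 100 people before exclusion:

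- examinable cases = 3.54 × (1 − u × k)
- routine rate = examinable cases / (1 − u), as all unexaminable people are found and excluded
- tiered rate = examinable cases / (1 − 0.5u), as unexaminable non-high-risk people stay in the denominator but are never tested

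| | u = 5%, k = 2 | u = 10%, k = 3 |
|---|---|---|
| Examinable cases | 3.54 × 0.90 = 3.186 | 3.54 × 0.70 = 2.478 |
| Routine | 3.186 / 0.95 = 3.35% | 2.478 / 0.90 = 2.75% |
| Tiered | 3.186 / 0.975 = 3.27% | 2.478 / 0.95 = 2.61% |
| Tiered minus routine | −0.09 points | −0.14 points |
| Either arm, failures kept and counted as not detected | 3.19% | 2.48% |

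The last row shows two things. Keeping the failures removes the artificial gap, because both arms then have the same numerator and denominator. It also shows that exclusion raises the routine rate (3.35% against 3.19% in the first scenario).

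**Wider range.** With u from 2% to 10%, risk 1 to 3 times that of examinable people, and 30–80% of the unexaminable classed high-risk, the tiered rate is lower by 0.01 to 0.26 points. The gap persists when unexaminable people carry only average risk, because it comes from untested people remaining in one denominator and not the other.

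**Sensitivity, routine arm.** Under the same assumptions, excluding failures gives 100%. If unexaminable cases count as missed, it is 3.186 / 3.54 = 90% in the first scenario and 2.478 / 3.54 = 70% in the second.

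**The case against.** The strongest reply is that section 2.3 lists enrolment criteria and does not say they are established by attempting the tests. Poor cooperation, a known corneal opacity or a recorded advanced cataract can be judged in any arm. The article does not state the order of recruitment, eligibility assessment and allocation, and the full protocol may. Section 2.9 specifies multiple imputation, and nothing says that enrolled people with ungradable images are dropped.

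Part of this stands. A reader might infer that the criterion can be applied to nobody in the control arm. That goes too far, since known conditions can be recorded there. But no history-only procedure is described, and in the other arms history would be supplemented by testing. A uniform examination before allocation would contradict Table 1 and the account of the control arm in section 2.4. Imputation and inverse probability weighting deal with missing data among enrolled people, not with people ruled ineligible. The recall of 10% of screen-negatives is a verification sample, and the closing offer to controls ("At the end of the study period, a comprehensive ophthalmic screening will be uniformly offered to all participants in the control arm") comes too late to define eligibility.

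Two other strong readings also fail.

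- **A spurious advantage for tiered screening.** A reader might compare underlying prevalence among those left in: in the first scenario, 3.54% control, 3.54 × 0.95 / 0.975 = 3.45% tiered and 3.35% routine. But the endpoint is confirmed glaucoma, not prevalence. Unexaminable non-high-risk people in the tiered arm are not tested, so the sign reverses. Nor is 3.54% the control rate, because detection there is passive.
- **Inflated specificity.** This does not follow. If failures count as not detected, unexaminable people without glaucoma become true negatives, and keeping them raises specificity. The effect depends on how failures are classified.

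**Conclusion.** The concern holds in a limited form. Apart from conditions known from history or records, criterion 2 as written would exclude at different rates by arm, so the detection-rate denominators are not comparable. Excluding test failures also inflates sensitivity. No claim is made about specificity.

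The size cannot be derived from the documents, because the unexaminable share, its glaucoma risk and its high-risk fraction are all assumed. On the main assumptions the bias runs against tiered screening by about 0.09–0.14 points, roughly a tenth to a seventh of the planned 1.0-point difference. For contrasts with the control arm, exclusion favours the routine arm relative to counting its failures as not detected. The net effect there cannot be quantified, because passive case-finding has no stated rate.

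**What to change.** 1. Base eligibility only on information obtainable identically in all arms (age, consent, questionnaire-reported or recorded history), and fix it before the community's allocation is disclosed.
2. Keep enrolled people with failed pressure measurement or ungradable images in the denominators. Record test failure as a screening outcome, counted as not detected unless glaucoma is confirmed, and report the failure rate by arm.
3. Apply the same principle to criterion 3, which also relies largely on an examination or a known history.
4. Reconcile the sentence on uniform data collection in section 2.4 and the one on yearly testing in section 2.6 with Table 1 and with the description of the control arm.

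The cost is amended eligibility wording and lower detection and sensitivity figures, by an amount that depends on the failure rate. No extra examinations are needed.

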All participants who enter the Tier 3 screening stage will undergo further examinations for definitive diagnosis, including standard automated perimetry for visual field testing, optical coherence tomography (OCT) imaging of retinal nerve fiber layer (RNFL) thickness, and gonioscopy to distinguish open-angle from angle-closure glaucoma. The final diagnosis will be made independently by two glaucoma specialists following a comprehensive review of all clinical data, with reference to internationally accepted diagnostic criteria for glaucoma, namely the presence of characteristic glaucomatous optic neuropathy with corresponding visual field defects, after excluding other ocular or neurological conditions that may cause optic neuropathy. Any diagnostic disagreement between the two specialists will be resolved by a third senior glaucoma expert who will make a final determination. To correct for verification bias, a random sample of 10% of participants who are screen-negative will also be recalled to undergo the same reference standard examination. Sensitivity and specificity of the two screening strategies will be calculated based on all screen-positive participants and the randomly selected screen-negative subset, with appropriate weighting to account for the sampling fraction.

The study is scheduled to begin patient enrollment in October 2025, with follow-up and final data collection expected to be completed in December 2032.

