To address potential parallel non-study eye care, a standardized procedure will be established to systematically collect information on all external ophthalmology encounters across all study arms at each follow-up time point. This will include optometry visits, outpatient consultations, and hospital admissions occurring outside the protocol, along with details of the healthcare facility, conducted examinations, principal findings, and clinical recommendations. These data will be incorporated as important covariates in the statistical analyses to evaluate the potential diluting or confounding effects of parallel care on the estimated effectiveness of the organized screening strategies, and sensitivity analyses will be conducted to assess the magnitude of such effects.

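### Glaucoma diagnosed outside the programme counts towards the detection rate in the control arm only, so each screening-versus-control contrast is biased against screening

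*Protocol article*

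**What the plan says.** Four parts of the protocol article bear on this.

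- **Section 2.6 (Follow-ups and outcome variables)** defines the detection rate as the proportion of each arm found to have the disease in one or both eyes. The diagnosis counts "as determined by the reference standard examination in the screening arms or by passive case-finding through medical records in the control arm". This is the main endpoint. Sensitivity, an additional primary outcome, is the share of confirmed cases "who are correctly identified by the screening protocol".
- **Section 2.3 (termination criteria)** covers participants in any group who are "diagnosed with glaucoma through screening or self-visit, they will be recorded and removed from the screening program". They then enter chronic disease follow-up.
- **Section 2.4 (Grouping schemes)** plans to "systematically collect information on all external ophthalmology encounters across all study arms at each follow-up time point". It gives the use of this information as follows: "These data will be incorporated as important covariates in the statistical analyses". Sensitivity analyses of parallel care are added. External diagnoses are not named as outcome events.
- **Section 2.2 (Study design)** verifies screen-negatives by sampling: "a random sample of 10% of participants who are screen-negative will also be recalled to undergo the same reference standard examination". Both accuracy measures (sensitivity and specificity) are then "calculated based on all screen-positive participants and the randomly selected screen-negative subset, with appropriate weighting to account for the sampling fraction". When the sample is drawn is not stated.

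**The concern.** A diagnosis made at a self-visit counts as a detected case if the participant lives in a control community. Read literally, it does not count if the participant lives in a screening community, although it is recorded in both. The difference between arms then mixes the effect of screening with a difference in what is counted.

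Section 2.4 includes the control arm to show the clinical and economic value of routine screening, and section 2.6 makes the incremental cost per additional case detected part of the primary economic outcome. Both depend on this contrast.

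A related question arises for sensitivity. Someone who screens negative and is later diagnosed elsewhere leaves the programme. Whether that person is still represented in the sensitivity estimate depends on how and when the recall sample is drawn.

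**Working it through.** **1. The plan's own figures, used here only for scale.** Section 2.5 assumes 3.54% versus 4.54%, two-sided α of 0.05 and 80% power. The continuity-corrected two-proportion formula gives 6,283 per arm, as stated. Then 6,283 × 1.20 = 7,540, and 7,540 / 0.80 = 9,425. These figures reproduce and are not disputed.

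**2. Detection contrast with control.** For one screening arm, let

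- d = proportion confirmed through the programme,
- x = proportion diagnosed externally and not through the programme,
- c = proportion diagnosed passively in the control arm.

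Contrast as defined: d − c. 
Contrast with one definition in both arms: (d + x) − c. 
Difference between them: −x.

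A limiting case shows the direction. Suppose a programme found nothing (d = 0) and self-visits went on as in control (x = c). The like-for-like contrast is 0, but the contrast as defined is −c, so a useless programme would appear to reduce detection. In practice screening pre-empts some self-visits. If it does not increase external visits, x lies between 0 and about c.

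The documents give neither x nor c. For assumed values of x, with 7,540 analysed per arm:

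| Assumed x | Cases left out |
|---|---|
| 0.25 points | 0.0025 × 7,540 ≈ 19 |
| 0.50 points | 0.005 × 7,540 ≈ 38 |

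The value of x need not be the same in the two screening arms. Table 1 schedules IOP and photography at years 0, 3 and 6 in the routine arm, yearly for tiered high-risk participants and never for tiered non-high-risk participants. The two contrasts with control may therefore be biased by different amounts.

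**3. Cost per additional case.** With incremental cost held fixed, the ratio is overstated by the factor (Δ + x)/Δ, where Δ = d − c. Taking Δ = 1 point purely as a scale, x = 0.25 gives 1.25/1, or 25% too high, and x = 0.50 gives 1.50/1, or 50% too high.

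**4. Sensitivity, conditional on timing.** Suppose a share s of missed cases has left before the recall sample is drawn, and the sampling frame excludes them. Then

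apparent sensitivity = Se / [Se + (1 − Se)(1 − s)].

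| True Se | s = 10% | s = 40% |
|---|---|---|
| 70% | 0.70/0.97 = 72.2% | 0.70/0.88 = 79.5% |
| 60% | 0.60/0.96 = 62.5% | 0.60/0.84 = 71.4% |

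Both Se and s are assumptions. If the sample is drawn and examined promptly after the screen, s = 0 and apparent sensitivity equals true sensitivity.

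**The case against.** **The powered comparison is tiered versus routine, and both arms use the same definition.** This stands. The endpoint is described as the detection rate of the screening protocol, and crediting each screening arm with what its protocol finds is coherent for that comparison. A reader might infer that the sample size or the main tiered-versus-routine test is undermined. The documents do not support that.

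**The bias is conservative.** It does run against screening. But conservatism is no protection for an economic ratio or for an estimate of what screening adds.

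**Self-visit cases may be counted anyway.** Section 2.4 says follow-up outcomes are collected uniformly, and section 2.6 plans RNFL measurement and perimetry for suspected or confirmed cases. Neither statement sends a self-visit case through the two-specialist reference diagnosis or places it in the numerator. Covariate adjustment for external visits does not repair a numerator that leaves cases out.

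**Removal from the programme is not removal from the analysis, and the weighting stands in for unsampled misses.** This is right, and it limits the sensitivity point. A reader might infer from sections 2.2 and 2.3 together that known misses are dropped and sensitivity is always inflated. That needs a delayed recall and a frame that excludes diagnosed participants, and the article states neither.

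**An external diagnosis is not necessarily a missed case.** This also stands. Up to three years separate routine-arm examinations, so some of these diagnoses will be new disease. Counting each as a false negative with full weight would mislabel incident cases, to a different extent in arms with different intervals.

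**Conclusion.** The main-endpoint definition in section 2.6 uses different numerators in the screening and control arms. Followed as written, it understates each screening-versus-control difference by the proportion of that screening arm diagnosed only externally, and it overstates the cost per additional case. The direction follows from the definitions. The size cannot be derived from the document: the 19 to 38 cases and the 25% to 50% are illustrations under stated assumptions.

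For sensitivity the conclusion is conditional. Overstatement of about 2 to 11 points arises within the assumed ranges if removed cases are missing from the recall frame, and none arises if recall promptly follows the screen. Unconditional inflation is not established.

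**What to change.** 1. **Contrasts with control, and the cost per additional case for those contrasts.** Define the endpoint as glaucoma diagnosed by any route, programme or external record, in all three arms. Apply the same record criteria and the same time window, and state whether cases found at the control arm's end-of-study examination fall inside that window.
2. **Tiered versus routine.** Keep cases detected by the screening protocol as the endpoint.
3. **Recall sample.** State that the 10% is drawn at each screen from all participants negative at that screen, including any later diagnosed externally.
4. **Diagnoses between screens.** Report them separately as interval cases, as a measure of programme sensitivity with a stated time window, rather than automatically as false negatives.

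Fix these definitions before outcome data are seen. External encounters and self-visit diagnoses are already to be recorded in every arm, so no new participants are needed. The cost is some extra record review by the existing specialist panel, plus tying the recall draw to each screen.
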